#### Health and service outcomes (medial)

The effectiveness of SchoolHealth on guideline recommendation goals will be measured through students' health and service outcomes (Table 3) [36–38] relevant to the guideline goals.

*Identification of vulnerable students* in need of follow-up will be captured qualitatively and assessed quantitatively through school nurses' evaluation of students' physical, psychological, and social functioning, registration of follow-up group, the number of follow-ups during the school year, and the student's self-reported mental health [The Strength and Difficulties Questionnaire (SDQ)] [39].

Students' health outcomes will be assessed by *somatic symptoms* (The Children’s Somatic Symptoms Inventory) [40], *quality of life* (Kidscreen-27) [41, 42], *general self-efficacy* [General Self-Efficacy scale (GSE-5)] [43, 44], and *health literacy* (Health Literacy for School-Aged Children) [45] at the start (T1) and end of the school year (T3). Health literacy and self-efficacy will also be measured post-consultation (T2), and health literacy will be explored qualitatively. Students will assess their *health behaviors* through items on behaviors of sleep, physical activity, nutrition, and screen time activities.

Students' assessments of *School environment and attendance* will be measured through a mix of self-developed questions and questions used in similar studies ([46], see Supplementary file 1 for details).

*User satisfaction* is an overall assessment of students' experiences (qualitatively) and degree of user satisfaction and empowerment in consultation (quantitatively). It includes items of involvement in consultations (like being heard and talking about what matters to them) and student-school nurse alliance, informed by both students and school nurses. The items are partly self-developed, inspired by similar scales [47, 48].

School nurses and school personnel will assess *interprofessional collaboration* between the school and school nurse [49]. School nurses will complete an assessment on their work-related self-efficacy using an adjusted version [50] of the GSE-5 [44].

#### Determinants

*Implementation determinants* will be measured to investigate their influence on fidelity to guidelines and guideline effects. These include school nurses' and leaders' assessments of implementation climate (Implementation Climate Scale) [36–38, 51], implementation leadership (Implementation leadership Scale) [52, 53], implementability of guidelines (Feasibility of Intervention Measure, Acceptability of Intervention Measure, Intervention Appropriateness Measure) [54], fidelity to implementation elements, implementation capacity (qualitative interviews), and school nurses' work-related self-efficacy [50].

*Background variables* will be collected from school nurses and teachers regarding age, gender, education, and years of work experience. Additionally, context characteristics will be assessed by school nurses. Students' assessment of *demographics* includes items on socioeconomic status, gender, and ethnicity. Other student-determinants will be assessed by mental health (SDQ) [39], self-efficacy [44, 55], and user satisfaction as described under Health and Service Outcomes.

#### Health data and linkage with national registers

Student questionnaires in GuideMe and the Young-HUNT4 Survey cover overlapping topics and identical instruments, subscales, or items. Both include for example the SDQ, items about general health and quality of life, health care use, and health behavior.

From the national registers, data on socioeconomic status, along with use of the school health services (KPR), general practitioners (KPR), physiotherapists (KPR), and specialized healthcare services (including psychiatric care) (NPR) will be linked to GuideMe data.

### Recruitment

The schools and school health services will be invited mainly through a convenience sampling approach.

#### School health services

Recruitment of school health services will be done through oral and written information and meetings with the leaders of the services. Additionally, written information will be provided to administrative leaders of the local municipalities.

#### Schools

Two different approaches will be used to invite schools: (1) After the school health services have agreed to participate or (2) simultaneously. A brief description of the study will be sent to the school leaders, with an invitation to attend an information meeting. The study will then be presented to the school principals and the school health services in each location. The interested schools will be asked to nominate a key contact person. School health services and schools agreeing to participate sign a cooperation agreement.

#### 8th grade students

Students in the participating classes and their parents will be introduced to the study via class visits by school nurses and parent meetings. The schools will provide parents with written information and a link to a digital informed consent form, including a voluntary option for providing the second parents' e-mail so that s/he can get information that the parent has consented to the student participating in the study. For students to participate in the study, at least one of the parents must complete an electronic consent form. The students will be given age-appropriate written and animated information at school. The students will consent to participate by filling in the questionnaire. A project webpage (https://guideme.rbup.no/en) is developed to enhance communication with all participants.

The recruitment of participants will be reported per the Consolidated Standards of Reporting Trials (CONSORT) guidelines for clustered randomized trials.

### Inclusion and exclusion criteria

Inclusion criteria are students who agree to participate, have informed consent from one of their parents, and are able to answer the web-based questionnaires.

The main exclusion criteria are intellectual disability or language problems, defined as not being able to complete the questionnaires. In addition, long-term school absenteeism may also be an exclusion criterion but will be considered individually. The reasons for exclusion will be documented in the CONSORT flowchart.

### Randomization in the factorial experiment (i)

The schools will be randomly assigned to test different combinations of the three implementation elements in SchoolHealth. The school randomization procedure will be carried out in R using a function specifically written for the GuideMe study. The function is developed by a statistician in collaboration with key personnel in the project and will be witnessed by an objective third party. The schools will be randomized to one of the eight experimental conditions (see Table 2).

### Power analysis and sample size in the factorial experiment (i)

An R-package called MOST developed for power analyses in factorial trials will be used (see supplementary file 2 for R-script). When conducting a factorial trial, one option for specifying effect size for power calculation is deciding the smallest effect of practical interest [56]. This can be decided using Cohen's rule of thumb [57].

We selected the following statistical attributes: α = 0.05, an effect size of d = 0.30, and statistical power of 0.80 (β = 0.20). Being a cluster trial, the design effect may affect our power calculation. Thus, an intraclass correlation coefficient (ICC) of 0.05 and an average size of clusters = 30 (SD = 15) was also accounted for [58]. The results from the power calculations indicated that 36 schools and 1080 students were needed in the study. To account for possible dropout and the need for subgroup analyses, we aim to recruit approximately 40 schools and 1200 students.

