**Methods:**

The GuideMe study is a factorial cluster randomized controlled trial examining SchoolHealth's effectiveness on guideline fidelity and guideline effectiveness goals. Forty Norwegian secondary schools will be randomized to eight different combinations of the elements in SchoolHealth. Participants will include school nurses and school personnel from these schools, and 8^th^ grade students (*n* = *1200).* Primary outcomes are school nurses' fidelity to the guidelines and student's ability to cope with their life (i.e., health literacy, positive health behaviors and self-efficacy). Quantitative methods will be used to test effects and mechanisms, while mixed- and qualitative methods will be used to explore mechanisms, experiences, and other phenomena in depth. Participants will complete digital questionnaires at the start and end of the schoolyear, and after the consultation during the schoolyear. The study will run in two waves, each lasting for one school year. The multifactorial design allows testing of interactions and main effects due to equal distribution of all factors within each main effect. Sustainment and scale-up of optimized SchoolHealth elements using national infrastructure are simultaneously prepared.

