#### The randomized factorial experiment (i)

We will employ a stratified, randomized cluster factorial design to evaluate the effects of the three implementation elements separately and in different combinations. The schools will be randomized to one of eight different experimental conditions.

The factors in Table 2 reflect the three previously described elements. The three elements are complementary, and together (yes/yes/yes) represent a blended implementation strategy that, in theory, should elicit the strongest outcomes based on an additivity or ecology principle (i.e., effects of implementation strategies are the sum of their parts or more than the sum of their parts, [9]. However, these implementation elements have rarely been evaluated independently or together. The multifactorial design allows for the testing of interactions and main effects due to the equal distribution of all factors within each main effect.

**Table 2 Tab2:** Experimental conditions in the factorial experiment

Experimental condition	SchoolHealth—Implementation elements		
	1. Digital feedback and administraton tool	2. Dialog support	3. Collaboration materials
1	Yes	Yes	Yes
2	Yes	Yes	No
3	Yes	No	Yes
4	Yes	No	No
5	No	Yes	Yes
6	No	Yes	No
7	No	No	Yes
8	No	No	No

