### Participants in qualitative interviews (ii and iii)

The qualitative data will be collected in both waves (Fig. 1). We will conduct individual interviews with 24 students and 12 school nurses, and focus group interviews with 12–24 school nurses, 12–24 teachers, and 6–12 school leaders. Variations in the experimental condition and geographic region will be emphasized when inviting participants to facilitate representativeness. The selection of students for qualitative interviews will be stratified [59]. When schools are selected, school nurses will provide names for students that fit pre-defined criteria regarding gender (boys/girls), quality of conversation in 8^th^-grade consultation (good/difficult), and cultural background (Norwegian/second culture).

School nurses, school personnel, and school leaders will be recruited through purposive availability sampling, emphasizing the participants` ability to elucidate a specific theme [60]. All participating nurses will be invited due to the limited number of participants and the large number of conditions. School personnel and leaders will be recruited to ensure representativeness to different experimental conditions, particularly element 3, Collaboration materials, due to their active role in this condition.

In Denmark, interviews with school nurses and teams implementing BørnUngeLiv.dk will be conducted. The main aim is to compare SchoolHealth with the Danish equivalent.

All interviews will be digitally audio-recorded and transcribed verbatim.

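### The 80% power behind 36 schools and 1080 students holds for student outcomes at ICC 0.05; it does not carry over to nurses' guideline fidelity, the first-named primary outcome

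*Protocol article*

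**What the plan says.** The abstract (Methods) names two primary outcomes: "Primary outcomes are school nurses' fidelity to the guidelines and student's ability to cope with their life". The Design section calls the study a hybrid type 2 trial, so fidelity and effectiveness both count.

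The section on power analysis and sample size gives one calculation, with α 0.05, d = 0.30 and power 0.80. On clustering it says that "an intraclass correlation coefficient (ICC) of 0.05 and an average size of clusters = 30 (SD = 15) was also accounted for". It concludes: "The results from the power calculations indicated that 36 schools and 1080 students were needed in the study". To allow for dropout and subgroup analyses, "we aim to recruit approximately 40 schools and 1200 students". The 0.80 is not tied to any outcome, and no number of nurses or school staff is given.

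Table 3 shows who reports fidelity:
- **8th-grade consultation, T2:** adherence and quality from nurses and students; dosage and adaptations from nurses only.
- **Collaboration with schools, T1 and T3:** adherence and quality from nurses and teachers or school leaders; dosage from nurses only. Students are not informants.

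The only remark on how many nurses there are comes from the section on qualitative interviews: "All participating nurses will be invited due to the limited number of participants and the large number of conditions". Linear mixed-effects models are planned for both fidelity and guideline goals.

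**The concern.** The calculation counts students, yet it is presented as what the study needs. A reader will take 80% power at d = 0.30 to cover both primary outcomes.

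For collaboration fidelity there are no 30 student records per school, only a few staff reports. For consultation fidelity there are many records, but those from one school describe the work of the same nurse or few nurses, and the implementation elements act mainly on those nurses. The within-school correlation could well exceed the 0.05 assumed for students.

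The section on sustainment and scaling makes decisions about individual elements depend on the results. A non-significant fidelity effect, read against a stated 80% power, could count against an element when the trial could not reliably have detected a moderate effect.

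**Working it through.** **Inputs from the article:** d = 0.30, α = 0.05 (taken as two-sided), ICC 0.05, mean cluster size 30, SD 15 (coefficient of variation 0.5), 36 schools needed, about 40 planned. Half of the schools are at each level of each factor ("due to the equal distribution of all factors within each main effect").

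**Assumptions, not in the article:** reports per school, correlation r between T1 and T3, ICCs for fidelity, and d = 0.30 applied to fidelity.

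**Formula:** a main effect is a 1:1 comparison. With effective sample size N_eff, the noncentrality is λ = d·√N_eff / 2. Power comes from the noncentral t with (schools − 8) degrees of freedom unless stated. The detectable d is the value that gives power 0.80.

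**1. The article's own figure.** Design effect for unequal clusters = 1 + ((1 + 0.5²)·30 − 1)·0.05 = 2.825.
- 36 schools: N_eff = 1080/2.825 = 382.3, λ = 2.93, df 28, power 0.808.
- 35 schools: N_eff = 1050/2.825 = 371.7, λ = 2.89, df 27, power 0.796.

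So 36 schools and 1080 students reproduces.

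**2. Collaboration fidelity, 40 schools, d = 0.30.**

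| Scenario | N_eff | Power | Detectable d |
|---|---|---|---|
| One report per school | 40 | 0.15 | 0.91 |
| Two independent nurses per school (df 72) | 80 | 0.26 | 0.64 |
| One report, T1 adjustment, r = 0.5 (df 31) | 40/(1 − 0.25) = 53.3 | 0.18 | 0.79 |
| One report, T1 adjustment, r = 0.7 (df 31) | 40/(1 − 0.49) = 78.4 | 0.25 | 0.65 |
| Five nurse/teacher reports per school, ICC 0.2 | 200/(1 + 4·0.2) = 111.1 | 0.33 | 0.55 |

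For example, with one report per school λ = 0.30·√40/2 = 0.95.

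**3. Consultation fidelity, 40 schools, 1200 records.** A mixed model weights schools, so N_eff = Σ m/(1 + (m − 1)·ICC). A simple set of school sizes with mean 30 and SD 15 is 20 schools of 15 and 20 schools of 45, which gives N_eff = 300/(1 + 14·ICC) + 900/(1 + 44·ICC), with df 32.

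| ICC | N_eff | Power | Detectable d |
|---|---|---|---|
| 0.05 | 176.5 + 281.3 = 457.7 | 0.88 | 0.27 |
| 0.07 | 151.5 + 220.6 = 372.1 | 0.80 | 0.30 |
| 0.10 | 125.0 + 166.7 = 291.7 | 0.70 | 0.34 |
| 0.20 | 78.9 + 91.8 = 170.8 | 0.48 | 0.44 |
| 0.30 | 57.7 + 63.4 = 121.1 | 0.36 | 0.53 |

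Power falls below 0.80 just above ICC 0.07. The unweighted design effect of step 1 would give 0.65, 0.42 and 0.31 at ICC 0.10, 0.20 and 0.30. That is too pessimistic for the planned model, so those values are not used.

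**The case against.** The strongest reply is that nothing has been miscalculated. The figure reproduces, the effect size is offered as the smallest of practical interest without being tied to an outcome, and the R script in supplementary file 2, which was not available, may treat fidelity separately. That stands: the fault is in the scope of the claim, not its arithmetic.

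A reader might infer that the trial has only about 15% power for fidelity as a whole. The article does not support that.
- It never says that there are about 40 nurses. The remark about limited numbers concerns interview recruitment and gives no count.
- The 0.15 applies only to one unadjusted report per school. Collaboration adherence and quality also have teacher or school-leader reports and a T1 value.
- Consultation adherence and quality are also reported by students, so many clustered records can enter the mixed model. If their ICC really were 0.05, power would be about 0.88.

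It is also fair to say that d = 0.30 may be a modest target for a proximal outcome that the elements address directly, and that covariates and reporting rules are often left to an analysis plan.

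None of this restores 0.80 for collaboration fidelity. Every scenario above stays at or below about 0.33 at the only effect size that the article states. For consultation fidelity, the margin is gone just above ICC 0.07.

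**Conclusion.** The point holds as one of scope. The stated 80% power is sound for main effects on student-reported outcomes at ICC 0.05, but the article presents it as the requirement for the whole study, including a first-named primary outcome to which it does not carry over.

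For collaboration fidelity, power at d = 0.30 is about 0.15 to 0.33, with detectable effects of about 0.91 down to 0.55 SD. For consultation fidelity it cannot be settled from the article, because no fidelity ICC is given: about 0.88 at ICC 0.05, falling to 0.36 at ICC 0.30, with detectable effects from 0.27 to 0.53 SD.

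These figures rest on 40 schools, the assumed numbers of staff reports, r of 0.5 to 0.7, the assumed ICCs, and d = 0.30 being applied to fidelity. Whether supplementary file 2 covers fidelity could not be checked.

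**What to change.** In the section on power analysis and sample size:
- Say that the 0.80 refers to main effects on student-reported outcomes at ICC 0.05.
- State the expected number of nurses and reporting school staff, the unit of analysis for each fidelity measure, and an assumed ICC for fidelity.
- Give detectable effects over a range. On the assumptions above, these are about 0.55 to 0.91 SD for collaboration fidelity and 0.27 to 0.53 SD for consultation fidelity at ICC 0.05 to 0.30. Replace them once real nurse and teacher numbers are known.

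In the statistical methods, or in the analysis plan if one exists, use the T1 value as a covariate for collaboration fidelity. Report fidelity effects with confidence intervals, and describe non-significant results as inconclusive rather than as absence of effect.

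No extra schools or data collection are needed. The cost is wording and a less favourable stated figure for one of the two primary outcomes.

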### Participants in qualitative interviews (ii and iii)

The qualitative data will be collected in both waves (Fig. 1). We will conduct individual interviews with 24 students and 12 school nurses, and focus group interviews with 12–24 school nurses, 12–24 teachers, and 6–12 school leaders. Variations in the experimental condition and geographic region will be emphasized when inviting participants to facilitate representativeness. The selection of students for qualitative interviews will be stratified [59]. When schools are selected, school nurses will provide names for students that fit pre-defined criteria regarding gender (boys/girls), quality of conversation in 8^th^-grade consultation (good/difficult), and cultural background (Norwegian/second culture).

School nurses, school personnel, and school leaders will be recruited through purposive availability sampling, emphasizing the participants` ability to elucidate a specific theme [60]. All participating nurses will be invited due to the limited number of participants and the large number of conditions. School personnel and leaders will be recruited to ensure representativeness to different experimental conditions, particularly element 3, Collaboration materials, due to their active role in this condition.

In Denmark, interviews with school nurses and teams implementing BørnUngeLiv.dk will be conducted. The main aim is to compare SchoolHealth with the Danish equivalent.

All interviews will be digitally audio-recorded and transcribed verbatim.

### Implementation of schoolhealth

#### Quality assurance/Monitoring

We will monitor implementation quality by measuring implementation fidelity to ensure validity in experimental conditions. We conceptualize implementation fidelity similarly to guideline fidelity [25]. Measures of implementation fidelity are designed to index whether implementation in each condition is conducted as planned (e.g., content, structure, dosage, materials, absentees, turnover), whether any adaptations are fidelity consistent (done to maintain core functions in our theory of change) or fidelity inconsistent (drifting away in a manner unlikely to maintain core functions), and whether proximal functions of the implementation (e.g., increased self-efficacy related to using guidelines).

#### Measures of fidelity to implementation elements

To index fidelity to implementation elements, school nurses and school personnel will answer questions about the completion and quality of each element:

*Adherence and adaptations* will be assessed using questions at T3 about training and support received during the study. *Satisfaction* will be assessed by asking how satisfied s/he was with the elements in SchoolHealth, and whether s/he would recommend them to a colleague. To assess *functions*, we will analyze the change in self-efficacy and collaboration adherence from pre to post. The school nurses will also be asked whether and how the elements helped them carry out the 8^th^-grade consultation and cooperate with schools. School personnel in element 3 will be asked whether and how the material helped them cooperate with the school health services and how many collaboration meetings they completed.

In addition, project coordinators register information about implementation in all experimental conditions. For training and consultations, the following will be registered: attendance, time spent, content completed, significant events, adaptations to plans, adherence. For technical assistance requested during the study that is of relevance to experimental conditions, the following will be registered: participant, time spent, content/issue, significant events, turnover/sick leaves, and other adaptations.

### Sustainment and scaling

Planning and preparing for sustainment and scale-up have been part of the co-creation process from the start of the exploration phase of the study. The projects' collaboration with key stakeholders, institutions educating health nurses, and authorities lays the foundation for using national infrastructure and regional competence centers (RBUP and RKBU) in scaling up.

The Norwegian Healthnet serves as a hub for developing a plan for sustainment and scale of functions in the DFA. This partnership provides a fruitful platform for designing, establishing, and testing secure data collection directly from users by means of Helsenorge.no, the digital platform for user interaction between citizens and patients with health services and registries.

Should the ongoing consultation (Dialog support) be a significant contributor to important implementation mechanisms and effects, we will plan for further improvements, sustainment, and scale by establishing an implementation group at the national competence centers involved in the study. Also, a protocol describing the structure, methods, and content of the ongoing consultations will be developed and made nationally available for other institutions to adopt. The e-learning module will be made accessible for educational purposes to the master's programs in public health nursing and will serve as a resource for the clinical practice of public health nursing.

If the results indicate that Collaboration material provides value, the material will be further improved based on participant feedback. RBUP and RKBU will offer schools and school health services an introduction and access to the revised material, which will be included as part of RBUP and RKBU Central Norway's ordinary teaching- and service provision.

In summary, each element in SchoolHealth can be sustained and scaled independently of the other, or in more ecological combinations. The results of the study will inform decisions regarding plans and recommendations for sustainment and scale.

